### Stripping and shedding criteria

2.9

After enrollment, patients who meet one of the following criteria will be terminated from the trial. The stripping criteria: those who might fail to meet the inclusion criteria and have entered the study. Those who might to follow the prescribed treatment or incomplete data affecting the efficacy evaluation and safety evaluation. Those who might have used the different therapeutic methods prohibited by this protocol. Those who might change the treatment plan midway by themselves. The shedding criteria: the subjects with poor compliance and self-withdrawal during the course of treatment. Those who might display serious adverse events or in those in which complications might occur. Those who will be unable to continue the treatment for various reasons.

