### Participants and recruitment

2.3

The recruitment posters will be displayed in the hospitals and community. And the forward recruitment information will be posted on WeChat to recruit the potential participants for this study. The participants will be explained in detail about the potential benefits and services to be provided and the risks associated with participating in the study, including the possible associated adverse clinical outcomes with viscera massage therapy. An informed consent will be signed after reading carefully by each participant prior to the participation. On the consent form, participants will also be asked whether they agree to use their data even if they opt out of the trial. The participants will also be required to obtain permission for the research team to share relevant information with staff from the participating hospitals or regulatory agencies. The participants will receive 4 different courses of viscera massage therapy. The personal information of all the participants will be kept confidential by the researchers and used only for this study. The patients must properly understand and sign informed consent. The FBG and 2hPG will be used to potentially determine whether participants meet the inclusion criteria. Patients who met the criteria will be included in the study (Fig. 1).

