### Exclusion criteria

2.7

However, the subjects will not be able to participate in this trial, if they meet any of the below indicated criteria: Patients who have been diagnosed with diabetes or other endocrine diseases, such as thyroid disease being treated. Patients who have been diagnosed with acute cardio-cerebrovascular events or myocardial infarction within 6 months. Patients who have severe impairment of liver and kidney function (Alanine transaminase, Aspartate Aminotransferase >2 times the upper limit of normal value, abnormal serum creatinine). The patient was in ketosis or hyperosmolar state. The patient was unable to exercise or required to have a special diet due to physical illness. Patients who was withdrawal, refusal of treatment, and unwillingness to exercise diet intervention during treatment. Patients who have uncontrolled hypertension (systolic blood pressure ≥160 mm Hg, diastolic blood pressure ≥110 mm Hg). Patients who have participated in similar studies or plan to undergo surgery to lose weight. Patients who are pregnant.

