### Termination of the standard

2.8

After enrollment, the trial will be effectively terminated if one of the following symptoms occurs: the patients suffer from the severe side reactions that may occur during the course of the study (medical certificate issued by the observing doctor), and severe complications or deterioration of the subjects during the study period. The subjects request to willingly withdraw from the clinical study halfway. Patients who may be uncooperative and have poor compliance. In addition, if the conditions for the termination of the test must be met after being processed by the competent doctor in accordance with the standardized working procedure, the test will be terminated immediately. The researchers will keep a detailed record of the reasons and time of withdrawal of the participants from the study. Patients with the untreated time exceedingly at least 1/2 course of treatment will be able to enter the efficacy statistics and must properly maintain a random medical record number.

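### Sections 2.7 to 2.9 treat stopping treatment as leaving the trial and conflict on who enters the efficacy analysis, so the group comparison is open to selection bias

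*Protocol article*

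**What the plan says.** Four parts of the protocol article bear on who stays in the trial and who is analysed.

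- **Section 2.9 (Stripping and shedding criteria)** opens with "After enrollment, patients who meet one of the following criteria will be terminated from the trial". The stripping list includes "incomplete data affecting the efficacy evaluation and safety evaluation", use of prohibited therapies, and "Those who might change the treatment plan midway by themselves". The shedding list includes "the subjects with poor compliance and self-withdrawal during the course of treatment". A further ground on that list is "Those who might display serious adverse events or in those in which complications might occur", and the list also takes in anyone unable to continue for whatever reason. Only ineligibility discovered late is not an event after allocation.
- **Section 2.8 (Termination of the standard)** also names withdrawal, poor compliance and severe reactions as grounds for termination, and requires the reasons and time of withdrawal to be recorded. It then says: "Patients with the untreated time exceedingly at least 1/2 course of treatment will be able to enter the efficacy statistics".
- **Section 2.7 (Exclusion criteria)** lists, among conditions that bar entry, "Patients who was withdrawal, refusal of treatment, and unwillingness to exercise diet intervention during treatment".
- **Section 2.3 (Participants and recruitment)** says that on the consent form "participants will also be asked whether they agree to use their data even if they opt out of the trial".

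On measurement, section 2.11.2 takes blood twice, before the first treatment and following the last. Section 2.11.3 takes stool before and after the intervention, and section 2.11.1 takes body measures at the start and weekly. No visit is described for a person who has been terminated. Section 2.11.5 compares the groups by one-way ANOVA.

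**The concern.** The allocated groups are comparable only as allocated. If people leave the analysed set because of what happened to them during treatment, the two remaining groups can differ for reasons other than massage.

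Here the removal reasons are compliance, willingness to continue, adverse events and completeness of data. Each may be related to outcome, and each may occur at a different rate in the two arms. Both arms have daily contacts under section 2.10, but the massage arm carries an extra half-hour session each time. Section 5 concedes the lack of double-blind control, and no threshold for poor compliance is given in 2.8 or 2.9.

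The timing makes this more than a matter of analysis. If a terminated person is not seen at week 4, no later analysis plan can recover the glucose, HbA1c, HOMA-IR or stool result.

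**Working it through.** **1. The rules side by side**

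| Event after allocation | 2.7 | 2.8 | 2.9 |
|---|---|---|---|
| Withdrawal or refusal | bars entry | terminated | terminated (shed) |
| Poor compliance | bars entry (unwilling to follow exercise or diet) | terminated | terminated (shed) |
| Serious adverse event or severe reaction | – | terminated | terminated (shed) |
| Incomplete data | – | – | terminated (stripped) |
| Changed or prohibited treatment | – | – | terminated (stripped) |
| Part of the course missed | – | may enter efficacy statistics by a half-course rule | no such allowance |

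The 2.7 item concerns behaviour during treatment, so it cannot be assessed at entry. The half-course rule in 2.8 is written in terms of untreated time. Read literally, it admits people who missed at least half the course; it could also be meant to admit those who received at least half. On either reading, entry to the analysis depends on exposure after allocation, and 2.9 contains no matching provision.

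**2. Extra burden of massage**

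Reading the schedule in 2.10 as five days on and two off for four weeks: 5 × 4 = 20 sessions of 30 minutes, on top of the advice given to both arms.

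**3. The plan's own sample-size figure**

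Section 2.2 gives n = 36 without an effect size, SD, power or dropout rate, so it cannot be reproduced. Inverting d = √(2/36) × (z for α + z for power), with two-sided α = 0.05, gives d = 0.66 at 80% power and 0.76 at 90%. The step from 36 to 40 equals a 10% allowance: 36 / (1 − 0.10) = 40.

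**4. Possible size of the bias (loss rates and correlations are assumptions)**

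Suppose there is no true effect, and that in each arm the least favourable fraction δ is removed on a latent variable with correlation ρ to the outcome. The shift in an arm's mean is ρ × φ(z_δ)/(1 − δ), in SD units. The factor φ(z_δ)/(1 − δ) is 0.109 at 5% loss, 0.195 at 10%, 0.350 at 20% and 0.497 at 30%. The bias is the difference between arms. The standard error is √(1/n₁ + 1/n₂), with each n equal to 40(1 − δ).

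| Loss, massage/control | n | Bias, ρ = 0.3 | Bias, ρ = 0.5 | SE | Type I error |
|---|---|---|---|---|---|
| 10%/10% | 36/36 | 0 | 0 | 0.236 | 5.0% |
| 10%/0% | 36/40 | 0.058 | 0.097 | 0.230 | 5.7% to 7.1% |
| 20%/5% | 32/38 | 0.072 | 0.121 | 0.240 | 6.0% to 7.9% |
| 30%/10% | 28/36 | 0.091 | 0.151 | 0.252 | 6.5% to 9.2% |

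Example, 30%/10% with ρ = 0.5: 0.5 × (0.497 − 0.195) = 0.151; 0.151/0.252 = 0.60; P(Z > 1.96 − 0.60) + P(Z < −1.96 − 0.60) ≈ 9.2%. With ρ = 0 the bias is zero at any loss. The calculation keeps the SD at 1 after removal, so it is approximate.

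**5. Upper bound**

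In simulated null trials with 40 per arm, removing exactly the worst responders from one arm only gives 0.19 SD and a 15% false-positive rate for 4 removed, and 0.34 SD and 36% for 8 removed.

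**6. Numbers retained**

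Section 2.2 gives the estimate as 36 but then asks for more than 36 per group. With independent losses from 40 per arm, the probability that both arms keep enough is:

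| Loss | 36 or more in both arms | More than 36 in both arms |
|---|---|---|
| 5% | 91% | 74% |
| 10% | 40% | 18% |
| 15% | 7% | 2% |

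At 10% loss: P(at most 4 lost of 40) = 0.629 and 0.629² = 0.40; P(at most 3 lost) = 0.423 and 0.423² = 0.18.

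**The case against.** The strongest reply is that analysis sets belong in an analysis plan that is not shown, and that 2.8 does let some people with interrupted treatment into the efficacy statistics. Section 2.3 also suggests an intention to keep data from people who opt out.

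The second point stands in part: it would be wrong to say that only completers are compared. But the 2.8 rule selects on exposure, so the set is still chosen after allocation. The first point does not dispose of the matter. The article states a rule, termination from the trial, and gives no outcome visit afterwards. The consent sought in 2.3 shows that use of such data was foreseen, but the article states no analysis that uses it.

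Three stronger readings are tempting and are not supported:

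- **That the bias favours massage.** Controls also have daily advice contacts to miss and diet and exercise advice to ignore. Removing non-compliant controls would push the other way.
- **That harm is hidden.** Nothing says adverse events of terminated participants go unreported. Section 2.8 asks for a medical certificate for severe reactions and a record of the reasons for withdrawal.
- **That the 15% to 36% error rates are to be expected.** They require removal of exactly the worst responders from one arm. Follow-up blood is drawn only after the last treatment, so staff could not rank people on those results during the course; only the body measures are weekly.

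It is also fair to say that ordinary dropout, not just stripping, would reduce the numbers.

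**Conclusion.** The point holds. As written, sections 2.7 to 2.9 merge stopping treatment with leaving the trial, disagree on who enters the efficacy analysis, and leave week-4 outcomes unsecured for those terminated. The comparison is open to selection bias of unknown direction and size; the documents do not show that it is biased.

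The 0.06 to 0.15 SD and 5.7% to 9.2% figures depend wholly on the assumed unequal losses and on a correlation of 0.3 to 0.5. If removal is alike in both arms or unrelated to outcome, the bias is nil and the error rate is 5%. The sample-size margin is thin: at an assumed 10% loss, both arms keep enough with probability 40% or 18%, depending on whether 36 or more than 36 is needed. The matter should be settled before outcomes are collected, because missed week-4 measurements cannot be recovered later.

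**What to change.** Reconcile 2.7, 2.8 and 2.9 by separating stopping treatment from leaving the trial, without altering any clinical stopping rule.

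- Obtain the planned week-4 bloods, stool and body measures on every allocated participant who still consents, whether or not treatment was stopped.
- Make the main efficacy comparison all participants in their allocated arm, with a stated method for missing week-4 values.
- Keep the set left after stripping and shedding as a secondary per-protocol analysis. State the half-course rule of 2.8 clearly and confine it to that set.
- Include the adverse events of terminated participants in the safety report.
- Delete the item on behaviour during treatment from the entry exclusions in 2.7.

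The cost is an amendment, the effort to bring stoppers back for one visit that is already in the schedule, and possibly a slightly smaller estimated effect, since people who stopped treatment would count in their allocated arm.

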### Treatment programs

2.10

After being enrolled, 40 individuals will be treated with AM and healthy lifestyle intervention, with the other 40 individuals receiving only healthy lifestyle intervention. The main viscera massage techniques include rubbing the abdomen, kneading abdomen, vibrating abdomen, and pressing the abdomen. The main points to be considered will be Zhongwan (CV12), Shenque (CV8), Zhongji (CV3). The acupoint location that will be used refers to the 2006 National Standard of the People's Republic of China (GB/T12346-2006) “Acupoint Name and Location.” During the treatment, room temperature will be kept appropriate, with the environment quiet and tidy. The patient will be laid on their back, exposing the abdomen in a relaxed state. The doctor will sit on the right side of the patient. Firstly, the doctor will rub the entire abdomen clockwise with CV8 as the center, up to CV12, down to CV3, the left and right sides to the left and right meridians of the foot Taiyin Spleen meridian respectively, for 5 minutes. Next, the whole abdomen will be kneaded with both hands for 10 minutes. Then, CV12 will be vibrated with one hand with a frequency of >200 times per minute for 10 minutes. Then abdomen will be pressed with one hand on CV8, deeply while breathing in and gently while breathing out, for 5 minutes. Each treatment will last 30 minutes.

Lifestyle interventions will include diet, exercise, and other lifestyle advice and will be performed by combining pushing healthy lifestyle guidance information through Wechat application and giving face-to-face advice together daily.

All patients will receive the treatment once a day, with 2 days off every 5 days. The intervention will be conducted for 4 weeks.

### Evaluation indicators

2.11

#### Body composition measurements

2.11.1

Weight, BMI, waist circumference (WC), WHR, and WHtR will be measured by a special study nurse at the first day of the whole intervention and last day of every week. BMI was calculated using body weight and height measured with bare feet and in minimal clothing using a stadiometer and an electronic scale. Waist circumference will be measured at the body midsection (iliac crest), which is between the lowest point of the ribs and the highest point of the pelvis, while the participants were in a calm, exhaling position, with their legs 25 to 30 cm apart. Hip circumference will be measured at the horizontal circumference of the rear most prominent part of the hip. WHR will be calculated by WC/hip circumference. WHtR will be calculated by WC/height.

#### Blood sample

2.11.2

Blood samples will be taken from each participant twice—one before the first treatment, and the other following the last treatment. Measurements will include triglycerides, total cholesterol, low-density lipoprotein cholesterol, and high-density lipoprotein cholesterol, FBG, 2hPG, and HbA1c, fasting insulin and HOMA-IR.

#### Fecal samples

2.11.3

Fecal samples from the participants will be obtained before and after the intervention. Samples will be collected using the special feces collection kit. All fecal specimens will be stored in the fridge at –80 °C before and after the intervention, and then will be performed for 16S rRNA gene sequencing and metagenomic detection.

#### Quality control

2.11.4

The study quality management will be strictly carried out with reference to the Quality Management Standard for Drug Clinical Trials. The viscera massage therapy will be performed by special well-trained chiropractors. To ensure the time, intensity, and frequency of manipulation operations be relatively consistent and meeting the clinical standardization, a thorough training, practice, and assessment of the manipulation operation will be conducted before the start of the treatment.

#### Statistical method

2.11.5

SPSS23.0 statistical software will be used for statistical analysis for all the data generated. Chi-square test will be used for enumeration data. Paired *t* test will be used for the comparison of measurement data before and after the treatment. One-way analysis of variance (ANOVA) will be used for comparison between the groups, with *P* < .05 as difference and *P* < .01 as significant difference.

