**Methods and design::**

Eighty prediabetes individuals will be recruited for this study. Eighty prediabetes individuals will be divided into lifestyle intervention group and viscera massage + lifestyle intervention group by a simple random method. Each group will have 40 individuals. The manipulation of the viscera massage + lifestyle intervention group will be mainly carried out through rubbing the abdomen, kneading abdomen, vibrating abdomen, and pressing the abdomen, 30 minutes per time, once a day, with 2 days off every 5 days. Lifestyle interventions will be performed by combining pushing healthy lifestyle guidance information through Wechat application and giving face-to-face advice together daily. The lifestyle intervention group will receive healthy lifestyle intervention only. All the intervention will be conducted for 4 weeks. Weight, body mass index (BMI), waist circumference, waist-to-hip ratio, and waist-to-height ratio will be measured at the last day of every week. Triglycerides, total cholesterol, low-density lipoprotein cholesterol, high-density lipoprotein cholesterol, fasting blood-glucose, 2-hour post-meal blood glucose (2hPG) and glycosylated hemoglobin, fasting insulin and insulin resistance index will be tested at the first day and last day of the intervention course. The fecal samples of subjects will be gathered at the first day and last day of the intervention course and will be performed 16S rRNA gene sequencing and metagenomic detection. Finally, the effect and potential mechanism of viscera massage on prediabetes will be discussed in combination with all the results.

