### Objectives

2.1

To determine the possible effects of viscera massage on prediabetes and to investigate the role of gut microbiota in improving prediabetes.

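### One uncorrected P < .05 rule covers all data, including the sequencing data, and no named test links microbiota change to glycaemic change

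*Protocol article*

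**What the plan says.** The objective (section 2.1) has two parts: the effect of viscera massage on prediabetes, and "to investigate the role of gut microbiota in improving prediabetes".

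Section 2.11 lists the evaluation indicators in three groups: body composition, blood and stool. For stool, section 2.11.3 states "Fecal samples from the participants will be obtained before and after the intervention" and that the specimens "will be performed for 16S rRNA gene sequencing and metagenomic detection".

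Section 2.11.5 closes the same block with one analysis rule: "SPSS23.0 statistical software will be used for statistical analysis for all the data generated". Apart from chi-square for counts, two tests are named. A paired t "test will be used for the comparison of measurement data before and after the treatment" is the within-group test. For the other contrast, "One-way analysis of variance (ANOVA) will be used for comparison between the groups". P < .05 is called a difference, and P "< .01 as significant difference". No adjustment for the number of tests is stated, and sequencing data are not exempted.

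On how the mechanism will be concluded, the Abstract (Methods and design) says only that "the effect and potential mechanism of viscera massage on prediabetes will be discussed in combination with all the results".

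**The concern.** Sequencing gives many features per sample, usually sparse relative abundances that sum to a constant. Feature-by-feature t tests or ANOVA at a fixed .05 have no control over false discoveries and ignore the compositional structure. If the rule is followed as written, some features will be called changed even where nothing has changed.

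There are two further problems for the mechanistic aim.

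- The named tests examine microbiota and glycaemia separately. Two separate differences do not show that one explains the other.
- Section 2.10 gives lifestyle advice to both arms, and the Discussion itself says lifestyle interventions have been found to act through the gut microbiome. A before-after change within the massage arm therefore cannot be credited to massage. The between-arm comparison can address that.

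At stake is the credibility of half of the stated objective. The glycaemic and anthropometric results are not affected by this point.

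**Working it through.** **Inputs from the protocol article.** 40 participants per arm (section 2.2); stool and blood each sampled before and after the intervention (2.11.2, 2.11.3); thresholds .05 and .01 with no correction (2.11.5). With two groups, one-way ANOVA gives the same P value as the two-sample t test.

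**Plan's own figure.** The article gives no feature count, error rate or power for the sequencing data, so there is nothing to reproduce. Its only design figure is 36 per group, stated without effect size, SD or power. It cannot be reproduced, and the error-rate calculation does not depend on it.

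**Assumption.** m, the number of features tested, is not in the document. The range 10 to 200 is shown.

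**Step 1: false positives when all m features are null, one comparison per feature.** Expected count = m × α. Chance of at least one, if independent = 1 − (1 − α)^m.

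| m | Expected at .05 | Chance of any at .05 | Expected at .01 | Chance of any at .01 |
|---|---|---|---|---|
| 10 | 0.5 | 40% | 0.1 | 10% |
| 50 | 2.5 | 92% | 0.5 | 40% |
| 100 | 5 | 99.4% | 1 | 63% |
| 200 | 10 | >99.9% | 2 | 87% |

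For m = 100: 100 × 0.05 = 5; 1 − 0.95^100 = 0.994; 1 − 0.99^100 = 0.634.

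**Step 2: correlated features.** Taxa are not independent, so the between-group test at .05 was simulated with 40 per arm, equally correlated null features and 2,000 runs.

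| m | Correlation | Mean number false | Chance of any | Chance of any with Benjamini-Hochberg at 5% |
|---|---|---|---|---|
| 50 | 0.3 | 2.49 | 81% | 4.7% |
| 50 | 0.6 | 2.39 | 53% | 3.2% |
| 100 | 0.3 | 5.08 | 94% | 4.8% |
| 100 | 0.6 | 4.90 | 65% | 2.8% |
| 200 | 0.3 | 10.01 | 99.6% | 4.2% |
| 200 | 0.6 | 10.00 | 77% | 3.1% |

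Correlation lowers the chance of any false feature but leaves the expected count near m × 0.05. Across all settings run, including independence, Benjamini-Hochberg held the chance of any false feature at about 3% to 6%.

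**Step 3: can separate tests support a mechanism?** Suppose massage shifts both a taxon and glucose by a standardised 0.66, with the two unrelated within arms. The value 0.66 is illustrative: it is the effect that 36 per group would detect with 80% power at two-sided .05. Power at 40 per arm is 0.839 by the normal approximation, so both between-arm tests are significant with probability about 0.839² = 0.70. Simulation with t tests (2,000 runs) gave 0.684. In about 68% of such trials both results look positive although the taxon and glucose are unrelated within arms.

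**Step 4: timing.** Stool and blood are collected at the same two points, so the data cannot show which change came first.

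**The case against.** The strongest defence is that section 2.11.5 never mentions taxa or sequencing. Its wording suits clinical measurements, and the unit of analysis could be a diversity index or a few named genera; the Introduction names only two organisms. Bioinformatics detail is commonly left to a full protocol or analysis plan, and neither is shown. This stands in part. The absence of a pipeline is not a fault here, and with 10 features the chance of any false finding is 40%, not near-certainty. It does not dispose of the point, because the article fixes a rule for all data and places it at the end of the block that lists sequencing.

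A reader might infer several stronger things that the document does not support.

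- *That false taxa are guaranteed, or more than 99% likely.* This needs about 100 or more features and independence. The count is not given and independence is implausible.
- *That two within-arm tests and one between-arm test triple the false findings.* That holds only if nothing changes in either arm. If lifestyle advice shifts the microbiota, within-arm changes are real but not specific to massage, and should not be counted as chance.
- *That nothing in the plan addresses massage.* The between-group ANOVA does, since both arms receive the lifestyle intervention.
- *That a list of taxa will be presented as the mechanism.* The text speaks of exploring and discussing a potential mechanism.
- *That the trial cannot inform the mechanism at all.* The limit lies in the named tests. The collected data would permit an association or exploratory mediation analysis.

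**Conclusion.** The point holds as a fault in the stated rule. Taken literally, section 2.11.5 applies uncorrected t tests and ANOVA to sequencing features. The expected yield under the null is about 5 per 100 features per comparison at P < .05 and 1 per 100 at P < .01. At 100 features the chance of at least one at P < .05 is about 99% if independent and about 65% to 94% at correlations of 0.6 to 0.3.

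These figures rest on an assumed feature count, on all features being null, and on reading the rule's scope as the words give it. The second part does not depend on the count: no named test connects microbiota change with glycaemic change, so the named analyses cannot meet the microbiota objective in section 2.1. Because the aim is described as exploratory, this is something that should be corrected before the sequencing data are analysed. It is not a flaw that undermines the trial.

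**What to change.** 1. In section 2.11.5, exclude the 16S and metagenomic data from the blanket rule and state their analysis separately.
2. Base microbiome inference on the between-arm contrast, adjusted for the participant's baseline sample. Report within-arm changes as description only.
3. For taxa and pathways, use a method suited to compositional data with false-discovery-rate control at a pre-stated level, for example Benjamini-Hochberg. The particular transformation, summary index, level and software are choices among defensible options, provided they are fixed before analysis.
4. Relate microbiota change to glycaemic change in a model that includes arm. Call the result association or exploratory mediation, since both are measured only at the same two time points.

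No visit, sample or participant is added. The cost is some analyst time and fewer taxa declared changed. The loss of power can be gauged from the stricter Bonferroni rule: at 100 features the threshold is 0.05/100 = 0.0005, the standardised difference detectable with 80% power at 40 per arm rises from 0.63 to 0.97, and power for 0.66 falls from 84% to 30%. False-discovery-rate control is less severe than that.

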### Setting

2.2

The patients will be recruited from the Department of tuina, Affiliated Hospital of Changchun University of Chinese Medicine, Hongqi First Community Health Service Center, Chaoyang District and Hongqi Second Community Health Service Center, Chaoyang District. Patients participating in the trial will be screened strictly according to the diagnostic criteria, inclusion criteria, and exclusion criteria. The sample size estimation will be based on the clinical calculation formula employed for small sample size. The estimate sample size is (n = 36). So, the therapeutic effect could be evaluated by the sample size of >36 in each group. In this study, 80 individuals will be recruited by simple random method and divided into two groups, 40 individuals in each group.

The researcher of the project will record the subject's basic information (such as date of birth, age, sex, and address) and answer questions patient involved in the trial. After completed the recruitment, individuals involved will be assigned a trial study serial number, also the patient's unique identification number, according to the order of enrollment, until the total numbers (n = 80) are all allocated. The odd-numbered individual was divided into the lifestyle intervention group, with the even-numbered individual the viscera massage + lifestyle intervention group. After clinical evaluation, blood and stool sampling, viscera massage therapy will be adopted.

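### Section 2.11.5 names paired before-after t tests and an unadjusted ANOVA without saying which carries the efficacy conclusion: the first cannot isolate massage, and the second leaves out the collected baseline

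*Protocol article*

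**What the plan says.** Section 2.11.5 (Statistical method) gives two procedures for measurement data. A paired t "test will be used for the comparison of measurement data before and after the treatment", and "One-way analysis of variance (ANOVA) will be used for comparison between the groups". Two thresholds follow: "with *P* < .05 as difference and *P* < .01 as significant difference". The section names no baseline covariate, does not say whether the ANOVA compares week-4 values or changes from baseline, and does not rank the two procedures.

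Other sections bear on this:

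- Section 2.11.2 (Blood sample) supplies a baseline for every blood outcome: "Blood samples will be taken from each participant twice—one before the first treatment, and the other following the last treatment". Section 2.11.1 does the same for the body measures, taken on the first day and then weekly.
- Section 2.3 makes two of the outcomes entry criteria as well: "The FBG and 2hPG will be used to potentially determine whether participants meet the inclusion criteria". Section 2.5 sets the IFG range at FPG above 6.1 and below 7.0 mmol/L, and also admits IGT with FPG below 7.0 and no lower FPG limit.
- Section 2.10 gives the lifestyle intervention to both arms; only massage differs.
- Section 2.2 has participants "divided into two groups, 40 individuals in each group", allocated by odd or even enrolment number.

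**The concern.** The trial asks whether massage adds anything to lifestyle advice. Only a comparison between the arms answers that. A before-after test within the massage arm measures the sum of massage, lifestyle advice, any time trend and, for outcomes used to select participants, regression to the mean. Two such tests placed side by side do not amount to a test of the difference between arms. Because section 2.11.5 gives neither procedure priority, a significant within-arm change could be reported as an effect of massage with nothing in the plan to prevent it.

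The between-arm test has a different weakness. With two arms, a one-way ANOVA is the unadjusted two-sample t test. Baseline is measured for every blood and body outcome, and the test as described makes no use of it as a covariate. In a trial of 80 people that can cost a useful amount of power, and it leaves any measured baseline difference between the arms uncorrected.

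**Working it through.** **1. The plan's own figure.** Section 2.2 estimates 36 per group and plans 40. It gives no effect size, SD, power or named formula, so 36 cannot be reproduced. Solved backwards for a two-sided 0.05 test of two means, d = √(2/36) × (1.960 + z_power). This gives 0.2357 × 2.802 = 0.66 SD at 80% power and 0.2357 × 3.242 = 0.76 SD at 90%. There is nothing in the document to compare these with.

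**2. Precision of the between-arm test.** Inputs: 40 per arm (section 2.2) and alpha 0.05 (section 2.11.5). Assumed: two-sided testing, a difference of 0.5 SD of the follow-up value, and a correlation r between baseline and follow-up, which the document does not give. Relative to comparing follow-up values, the variance of the arm difference is multiplied by 1 − r² for ANCOVA and by 2(1 − r) for change scores. Power comes from the noncentral t distribution, with d = 0.5 divided by the square root of that factor.

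| r | ANCOVA factor | 40 per arm works like, 40/(1 − r²) | Power, follow-up values | Power, change scores | Power, ANCOVA |
|---|---|---|---|---|---|
| 0.3 | 0.91 | 44 | 60% | 46% | 64% |
| 0.5 | 0.75 | 53 | 60% | 60% | 72% |
| 0.7 | 0.51 | 78 | 60% | 81% | 87% |

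ANCOVA has the highest power in every row, whichever way the ANOVA is read.

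**3. Regression to the mean in the paired test.** This was simulated for FBG with 40 per arm and no treatment, lifestyle or time effect. Assumed: everyone enters on 6.1 to 7.0 mmol/L, the screening value is the baseline, the true population mean is 5.6 to 5.9 mmol/L, the true SD 0.5, and the within-person SD 0.2 to 0.4.

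- The mean falls by 0.07 to 0.32 mmol/L.
- The paired t test gives P < .05 in about 36% to 97% of arms.
- The between-arm test on follow-up values rejects in about 5% of trials, as it should.
- If a separate baseline sample is drawn after screening, the same model gives a fall of 0.00.

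**4. What truncation at entry does to r for FBG.** Selecting on a narrow range lowers the correlation. In the model of step 3, r among those selected is about 0.26 to 0.59. At these values 1 − r² is 0.93 to 0.65, so 40 per arm works like 43 to 61, and ANCOVA power for 0.5 SD is 63% to 78%. The largest fall from regression to the mean and the largest gain from ANCOVA therefore do not occur together for FBG: where the fall is 0.32 mmol/L, power rises only from 60% to 63%.

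**The case against.** The plan does name a between-group test, and nowhere does it say that efficacy will be claimed from the paired tests. A reader might infer that effects will be judged within arms; the text does not say so. What stands is that it also does not exclude it, since neither test is given priority.

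A reader might also infer that regression to the mean distorts the ANOVA. It does not when the arms are comparable: the expected fall is common to both arms and cancels, as the 5% rejection rate in step 3 shows.

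The ANOVA might be meant for change scores, in which case it would use baseline. Section 2.11.5 leaves this open, so a flat statement that it ignores baseline goes too far. The precision point survives, because change scores are less precise than ANCOVA at each r checked, although at r = 0.7 the gap is only 81% against 87%.

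The size of the regression to the mean is conditional. Sections 2.3 and 2.11.2 do not say whether the screening sample and the pre-treatment sample are the same draw, and people entering on IGT have no lower FPG limit, so the FBG figure does not describe the whole sample. Nor does it extend to HbA1c, lipids or insulin, which are not entry criteria.

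Finally, a mixed model for the weekly measures, log transformation and a centre term are details that an analysis plan may properly settle. Their absence here is not a fault.

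**Conclusion.** The point holds in a limited form and should be fixed. Section 2.11.5 states its methods, so this is a choice made in the text and not a detail deferred elsewhere. It has two parts.

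- **Paired tests.** They cannot separate massage from the lifestyle intervention given to both arms; this needs no assumption. The added regression to the mean, 0.07 to 0.32 mmol/L for FBG, rests on the screening value serving as baseline, on entry by the IFG range, and on the assumed distributions.
- **Between-arm ANOVA.** It remains a valid test when the arms are comparable. What it loses is precision: at 0.5 SD and 40 per arm, 60% power on follow-up values against 64% to 87% with ANCOVA for r of 0.3 to 0.7, and 63% to 78% for FBG under truncated entry. The gain depends on r and is small when r is low.

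The documents do not support the stronger conclusion that the planned between-arm comparison would produce a false effect through this choice of test. Odd/even allocation is a separate fault that bears on whether the arms are comparable at all; adjusting for measured baseline values does not repair it.

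**What to change.** In section 2.11.5:

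1. State that efficacy claims on each continuous outcome rest on the between-arm difference at week 4, estimated by ANCOVA (week-4 value on arm and baseline value) and reported with its 95% CI.
2. Report within-arm changes descriptively, without P values, in place of the paired t tests.

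It would also help to say in section 2.11.2 whether the screening FBG and 2hPG serve as the baseline values or a separate sample is drawn.

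The cost is a few lines of text. The baseline values are already collected, and the named software fits ANCOVA. No further data or participants are needed.
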